### Sample size

Statistics from QLD and NSW in Australia in 2022 suggest there is a large population of P1 licence holders aged 18–20 years to sample from: 32,151 young drivers in QLD [38] and 42,039 in NSW [39]. Based on crash statistics for QLD from 2016 to 2022, the incidence of a young P1 licence holder having a police-reported crash of any type during a 6-month period is approximately 3% [40], with similar patterns expected across NSW and WA. Based on the findings of recent research [7, 8] the FEEDBACK trial intervention is expected to lower the proportion of a police-reported crashes from 3 to 1.5%.

To detect a 1.5% absolute reduction in the incidence of young drivers having a police-reported crash of any type during the 24-week intervention and post-intervention periods, from 3% in the control group to 1.5% in the intervention group (or 0.5 relative risk), using a two-sided type I error of 5% and a power of 80%, a total of 3,068 participants are required. Allowing for a 15% non-response rate due to drivers who may choose to withdraw from the study, turn off their phones, or delete the smartphone app, 1,805 participants per arm, or a total of 3,610 participants, will be recruited to participate in the trial.

To achieve adequate participant enrolment and reach the target sample size, recruitment strategies will be carried out in partnership with government stakeholders. The transport departments from the three states of Western Australia, Queensland, and New South Wales will assist with advertising the trial via several media channels, including social media, associated websites, and advertising boards in licencing centres.

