### Hypotheses and outcome measures

The **primary hypothesis** will assess whether personalised safety feedback and personalised financial incentives reduce the incidence of police-reported crashes of any type during the 24-week intervention and post-intervention periods. The primary outcome is a police-reported crash over the 24-week intervention and post-intervention periods. The research team will obtain data on police-reported crashes using drivers’ licence numbers provided by participants in the pre-trial questionnaire.

The **secondary hypotheses** will assess the effects of personalised feedback and financial incentives on:

Reducing the incidence of self-reported crashes by young drivers.Improving drivers’ safety scores (‘DrivePoints’ scores) from baseline.Reducing crash risk behaviours identified by speeding, harsh braking, hard acceleration, and drowsy driving from baseline.

The **outcomes** to assess the secondary hypotheses are:

Self-reported involvement in a crash that took place during the 24-week intervention and post-intervention periods that resulted in damage to their own or someone else’s vehicle.DrivePoints score at baseline and at weekly intervals through to week 28.Driving behaviours, namely:
Speeding (defined as 10 km/h over the speed limit).Harsh braking (sudden braking in which items in the vehicle would move around, defined in telematics technology as a -0.5 g force).Hard acceleration (rapid acceleration exceeding a 0.25 g force).

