#### Crash data

Police-reported crash data will be accessed through each of the three states’ respective Department of Transportation and will be used to assess the trial’s primary hypothesis. Participants’ licence numbers (collected in the pre-trial questionnaire) will be used to access police-reported crash data. Crash data obtained will include not only binary data, i.e., ‘yes/no’ data on whether a driver was involved in a crash, but also the number of crashes (if the driver was involved in more than one). Data will be obtained for all drivers – both the intervention and control groups – blind to group status.

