### Statistical analysis

A formal detailed statistical analysis plan will be written by the trial biostatistician and published on our research centre’s website while blind to group allocation. The analysis will include all participants according to their randomised allocation.

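### The single 80% power figure does not fit the trial's own outcome source and analysis set: the 15% allowance treats app leavers as lost outcomes, and a 6-month control risk is used for a 24-week window

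*Protocol article*

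**What the plan says.** The protocol article's Sample size section takes its control risk from Queensland crash statistics: "the incidence of a young P1 licence holder having a police-reported crash of any type during a 6-month period is approximately 3" per cent. It plans for a fall "from 3% in the control group to 1.5% in the intervention group (or 0.5 relative risk"), and states that, "using a two-sided type I error of 5% and a power of 80%, a total of 3,068 participants are required". It then allows for a "15% non-response rate due to drivers who may choose to withdraw from the study, turn off their phones, or delete the smartphone app" and arrives at 1,805 per arm, 3,610 in total.

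Three other sections bear on this:

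- **Hypotheses and outcome measures** sets the window: "The primary outcome is a police-reported crash over the 24-week intervention and post-intervention periods". The crash data are obtained through the licence number given before the trial.
- **Crash data** says of the police records: "Data will be obtained for all drivers", in both arms.
- **Statistical analysis** says: "The analysis will include all participants according to their randomised allocation".

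**The concern.** Dividing by 0.85 is right when 15% of randomised participants have no primary outcome. Two of the three causes named, turning off the phone and deleting the app, do not have that result. The crash record does not pass through the phone, so these drivers still have an outcome and still count in their assigned arm. What the app loses is the telematics on which the in-app feedback, the targets and the deductions are based. In the intervention arm, such drivers may move back towards control risk and pull the contrast towards the null. Extra numbers of the size 1/(1-d) do not make up for that.

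Separately, a risk observed over about 26 weeks is used unchanged for a 24-week window, which overstates the expected number of events.

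What is at stake is how a non-significant result is read. A reader told that the trial had 80% power to detect a halving of crashes will take a null result as stronger evidence than it may be.

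**Working it through.** **Inputs.** From Sample size: control risk 3% over 6 months, intervention risk 1.5%, two-sided 5%, 80% power, 15% allowance, 1,805 per arm. From Hypotheses and outcome measures: a 24-week window. From Randomisation and blinding: 1:1 allocation. The effect in drivers who stop using the app is not given, so it is an assumption, varied below from none to full.

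**1. The plan's own figures.** Two-proportion formula, pooled variance under the null, no continuity correction:

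n = [1.960 x sqrt(2 p(1-p)) + 0.842 x sqrt(p1(1-p1) + p2(1-p2))]^2 / (p1-p2)^2, where p is the mean of p1 and p2.

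With p1 = 0.03, p2 = 0.015, p = 0.0225: [0.4111 + 0.1763]^2 / 0.015^2 = 1,533.3, so 1,534 per arm and 3,068 in total. Then 1,534/0.85 = 1,804.7, so 1,805 per arm and 3,610. Both match.

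**2. Control risk for the actual window.** 3% x 24/26 = 2.77%. Halved, 1.385%.

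**3. Dilution.** If a share d of the intervention arm has no benefit and the rest have a relative risk of 0.5, the as-randomised relative risk is 0.5(1-d) + d. For d = 0.15 this is 0.575, that is 3% v 1.725%, or 2.77% v 1.59%. If the 15% keep half the effect (relative risk 0.75), it is 0.85 x 0.5 + 0.15 x 0.75 = 0.5375.

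**4. Power.** Power = Phi{[(p1-p2) sqrt(n) - 1.960 sqrt(2p(1-p))] / sqrt(p1(1-p1) + p2(1-p2))}. For 3% v 1.725% and n = 1,805: (0.5417 - 0.4210)/0.2146 = 0.562, giving 71.3%. All cases, with 1,805 per arm randomised:

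| What happens to the 15% | Control 3% | Control 2.77% |
|---|---|---|
| All linked; 0.5 is already the as-randomised effect | 86.0% | 83.1% |
| All lose their outcome (1,534 per arm left) | 80.0% | 76.7% |
| All linked; leavers keep half the effect | 79.3% | 76.0% |
| Half lose outcome, half linked with no effect | 75.5% | 72.1% |
| All linked; leavers at control risk | 71.3% | 67.8% |

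A Wald test on the log relative risk gives 70.1% and 66.6% for the last row, so the choice of test matters little.

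**5. How much dilution 80% can bear.** With everyone linked, power stays at 80% while d is below about 7% (3% risk) or about 3% (2.77% risk).

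**6. Inflation under full dilution.** 80% power would need 2,227 per arm (4,454) at 3%, or 2,417 per arm (4,834) at 2.77%. At 3% the factor is 2,227/1,534 = 1.45, against 1/0.85 = 1.18 used.

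**7. Detectable effect.** With 1,805 per arm analysed, the true as-randomised relative risk detectable with 80% power is about 0.53 (3%) or 0.52 (2.77%). This is not the significance threshold: an observed relative risk of about 0.66 or 0.65 already gives p < 0.05.

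**The case against.** The strongest reply is that the sample-size text compares the risk in the two groups over the whole 24 weeks, including four weeks with feedback and incentives off. That can be read as an as-randomised contrast with non-adherence already inside it. On that reading nothing is diluted further, and linking everyone gives 86% or 83%, above target. This stands, and it is why a shortfall cannot be asserted outright. It does not rescue the stated figure, though: on that reading app deletion calls for no inflation, and the power is not 80% either.

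Other parts of the reply also stand:

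- The 15% includes withdrawal from the study. The article does not say whether linkage continues after withdrawal, and the Primary outcome section foresees some missing data. For true losses, 1/(1-d) is correct.
- The 15% is applied to those recruited, and randomisation follows a 4-week baseline. Loss in that period cannot dilute.
- Targets, scores and account balance also go out by SMS, and Table 1 sets a target after a month without trips. Deleting the app need not end all exposure, so full reversion to control risk is the low end of the range.
- The 3% is labelled approximate, and the window correction costs only about 3 points. If all outcomes are linked and nothing is diluted, it leaves power above 80%.

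A reader might infer from the mismatch that the trial is shown to be underpowered, or that the sample-size arithmetic is wrong. The documents support neither. The arithmetic reproduces, and the shortfall depends on adherence and linkage assumptions that the article does not give.

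**Conclusion.** The concern holds as a mismatch between stated premises. At a 3% control risk, 80% is the right figure only if all 15% lose their crash outcome. The Crash data and Statistical analysis sections contradict that for drivers who merely stop using the app. Even on that premise, scaling the control risk to 24 weeks lowers power to 76.7%, and 1,665 rather than 1,534 evaluable per arm would be needed.

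The direction of the error depends on what 0.5 describes. Over the cases considered, power at 1,805 per arm runs from 71% to 86% at 3% control risk and from 68% to 83% at 2.77%. The top end needs 0.5 to be the as-randomised effect with complete linkage. The bottom end needs the whole 15% to be randomised, linked and without any benefit. All figures assume that the 6-month risk scales in proportion to time and that the other two states share the Queensland rate, as the article expects.

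**What to change.** Keep 3,610 and reword the Sample size section:

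1. Use a 24-week control risk of about 2.8%.
2. Split the 15% into (a) lost linkage, withdrawal with loss of the outcome, and loss before randomisation, for which 1/(1-d) applies; and (b) app non-use with the outcome retained, for which it does not. The whole 15% should not be re-labelled as discontinuation, because the article lists study withdrawal among its causes.
3. State whether the relative risk of 0.5 is the as-randomised effect or the effect in drivers who keep using the app.
4. Replace the single 80% with the range in the table, each figure tied to its assumption, and give the true as-randomised relative risk detectable with 80% power (about 0.53 at 3%, 0.52 at 2.77%).
5. State that crash linkage continues whatever the app status, unless consent to linkage is withdrawn.

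The cost is wording only, with no added participants. The drawback is that the stated power becomes a range that is mostly less favourable than 80%.

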### Randomisation and blinding

Following the 4-week baseline period, eligible drivers will be randomised to intervention or control using randomly permuted blocks of varying sizes in a 1:1 ratio, stratified by study site (state) and sex (male/female). The randomisation schedule will be computer-generated by an independent statistician and stored on a password-protected database at the University of Melbourne, managed by a researcher who is not one of the investigators. It will not be possible to blind participants due to the nature of the intervention. However, chief investigators will be blinded to group allocation during the statistical analysis. Main statistical analyses will be performed blinded to group details.

## Data and analysis

### Data collection

#### Pre-trial questionnaire

The pre-trial questionnaire will be disseminated online via Qualtrics, an online survey platform. It is composed of an introductory section, including copies of the plain language statement and informed consent form. Upon consent, participants will be asked to enter their driver’s licence number, mobile number, and email address. The questionnaire includes questions regarding demographics including [specify demographics], driving experience and attitudes to risky driving. Attitudes to risky driving questions were adapted from Iverson [41] and ask participants to rate their agreement with behavioural statements regarding rule violations and speeding, careless driving of others, and drink-driving. Attitudes to risky driving (ATRD) will be evaluated on a five-point Likert scale for each of the 16 ATRD items and summary ATRD scores calculated as the sum of all item scores, after all response data are re-coded so that higher-item scores indicate endorsement of higher-risk behaviours. Summary scores have a possible range of 16–80, with higher scores correlating with more frequent endorsement of higher-risk behaviours [8, 28, 41].

#### Post-trial questionnaire

The post-trial questionnaire includes the same ATRD items as the pre-trial survey and, additionally, it asks participants whether they were involved in any crashes during the 24-week intervention and post-intervention periods that resulted in damage to their own or someone else’s vehicle.

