#### Secondary outcomes

The DrivePoints score will be analysed using a constrained longitudinal data analysis (cLDA) model [42]. The response will consist of all DrivePoints scores (scores at baseline, at weekly intervals until 24 weeks post-randomisation) and the model will include factors representing treatment, time (categorical), and treatment-by-time interaction, with the restriction of a common baseline mean across treatment groups.

The total number of police-reported crashes of any type during the 24-week intervention and post-intervention periods will be analysed using a Poisson regression model. Whether a driver has a self-reported crash during the 24-week intervention and post-intervention periods will be analysed using a log-binomial regression model. Driving behaviours (i.e., binary outcomes – speeding, harsh braking, and harsh acceleration at baseline and at weekly intervals from week 4 to week 28) will be analysed using mixed-effects Poisson regression models with robust standard errors. All analysis models will be adjusted for stratification factors, study site and sex.

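### The self-reported crash outcome, as worded, does not exclude crashes in which the participant was not driving, so it is broader than its hypothesis about crashes by young drivers

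*Protocol article*

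**What the plan says.** All references are to the protocol article.

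- **Hypothesis** (Hypotheses and outcome measures): the relevant secondary hypothesis is "Reducing the incidence of self-reported crashes by young drivers".
- **Outcome** (same section): "Self-reported involvement in a crash that took place during the 24-week intervention and post-intervention periods", limited to crashes with damage to the participant's or another party's vehicle. There is a period and a damage threshold, but no statement of who was driving.
- **Instrument** (Post-trial questionnaire): "it asks participants whether they were involved in any crashes during the 24-week intervention and post-intervention periods that resulted in damage". This is a summary in indirect speech; the item itself is not reproduced.
- **Analysis** (Secondary outcomes): "Whether a driver has a self-reported crash during the 24-week intervention and post-intervention periods will be analysed using a log-binomial regression model". No exclusion by role is mentioned.
- **Police data, for comparison** (Crash data): records are reached through the participant's licence number, and the article speaks of "yes/no’ data on whether a driver was involved in a crash".

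**The concern.** The hypothesis is about crashes by drivers; the outcome is about involvement in a crash. The two differ whenever someone else is at the wheel. Take three answers scored on the outcome as written:

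1. The participant, driving, hits a parked car: counted, and within the hypothesis.
2. The participant is a passenger in a friend's car that crashes: fits the wording, outside the hypothesis.
3. The participant sits in their own car while a relative drives it into a post: fits the wording, outside the hypothesis.

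The intervention sections describe a score built from the participant's own driving and a monthly deduction tied to that score. Crashes of types 2 and 3 should therefore occur at much the same rate in both arms. Counting them adds a similar number of events to each arm and moves the risk ratio towards 1.

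This is a matter of data capture. If the item records no role, no later analysis rule can separate driver from non-driver crashes. Going back to participants would also be hard: the questionnaire is sent at the end of the post-intervention period, and the Confidentiality section has personal data destroyed after each participant's 28 weeks.

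**Working it through.** **Step 1. The plan's own figure.** The only sample size stated is for the police-reported outcome: "using a two-sided type I error of 5% and a power of 80%, a total of 3,068 participants are required". Inputs from the Sample size section are 3% against 1.5%, with 1:1 allocation. With pooled variance and no continuity correction:

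n per arm = [1.960 × √(2 × 0.0225 × 0.9775) + 0.842 × √(0.03 × 0.97 + 0.015 × 0.985)]² / 0.015² = 1,534 after rounding up

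The total is 2 × 1,534 = 3,068, and 1,534 / 0.85 rounds up to 1,805 per arm, or 3,610. Both stated figures reproduce. Neither depends on the self-reported outcome.

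**Step 2. The dilution formula.** Let *d* be the control-arm risk of a crash while driving and *e* the risk of a crash with someone else driving. Take *e* as equal in both arms, and ignore participants who have both kinds. Let *s* = *e*/(*d* + *e*) be the non-driver share of control-arm events, and *R* the risk ratio for driver crashes. Then

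observed risk ratio = (*R* × *d* + *e*)/(*d* + *e*) = *R* × (1 − *s*) + *s*

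The shift towards 1 is *s* × (1 − *R*). It vanishes when *R* = 1, so under no effect there is no bias; the problem is attenuation of a real effect.

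**Step 3. Illustration.** The documents give no *s*, and no rate or effect for self-reported crashes. The 0.5 is borrowed from the planning of the primary outcome; the values of *s* are assumptions.

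- *s* = 0: 0.50
- *s* = 10%: 0.5 × 0.9 + 0.1 = 0.55
- *s* = 20%: 0.5 × 0.8 + 0.2 = 0.60
- *s* = 30%: 0.5 × 0.7 + 0.3 = 0.65

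**Step 4. What this could do to power.** Two-sided 5%, 1,534 per arm, *R* = 0.5. The control-arm self-report risk is also an assumption, so three settings are shown.

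| Non-driver share *s* | All self-reported crashes 3% | Driver crashes 3%, others added | All self-reported crashes 10% |
|---|---|---|---|
| 0 | 80.0% | 80.0% | about 100% |
| 10% | 69.9% | 74.5% | 99.7% |
| 20% | 58.4% | 68.3% | 98.3% |
| 30% | 46.5% | 61.4% | 94.1% |

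The loss of power is marked if self-reported crashes are as rare as police-reported ones, and small if they are much more common. The attenuation in Step 3 is the same in every column.

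**The case against.** The strongest reply is that driver crashes were meant all along. The hypothesis names young drivers. The analysis section speaks of whether a driver has a self-reported crash. The Crash data section uses the same word, involved, for police records of drivers. All participants are enrolled as licensed drivers, and the phrase about their own or another vehicle can be read as a damage threshold covering the two parties to a collision. The item is only paraphrased, and the real questionnaire may already specify the driver.

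Much of this stands. A reader might infer that the outcome expressly includes crashes with someone else at the wheel. The documents do not support that: they fail to exclude such crashes, which is a weaker statement, and many participants may answer for their own driving anyway. A reader might also take the illustrated ratios as the expected loss. They are not; in Step 3 the lost fraction of the effect equals the assumed share by construction.

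What does not stand is that the analysis sentence settles the matter. The article calls every participant a driver, so asking whether a driver has a self-reported crash identifies the person, not their role in that crash. Nor is this simply detail left to a fuller document: the article states the outcome definition and repeats it for the questionnaire, and both times the limit is absent.

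**Conclusion.** The point holds as a gap in the outcome definition. As worded, the self-reported crash outcome is broader than its hypothesis because it does not exclude crashes in which the participant was not driving. Any that are counted would bias the self-reported risk ratio towards 1, provided that such crashes are largely unaffected by arm. The size cannot be derived from the documents.

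The reach is limited. One secondary outcome is concerned. It would go too far to conclude that the trial's main result is at risk: the primary outcome comes from police records linked by licence number, and the sample size is untouched. Nor do the documents say that the self-reported outcome is there to corroborate the primary one; it has its own hypothesis. This is a minor, inexpensive clarification.

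**What to change.** First check the live questionnaire item. If it already limits the answer to crashes while driving, only the article's outcome wording needs to follow. If not, add *while you were driving* to the item, or ask the participant's role in each reported crash and count only those as driver. In either case, define the outcome under Hypotheses and outcome measures as self-reported crashes in which the participant was the driver, and word the Post-trial questionnaire section to match.

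The cost is a few words or one extra question in an online form, a minor questionnaire amendment, and slightly fewer events counted. The events lost are those outside the hypothesis.

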#### Telematics and DrivePoints

The FEEDBACK app will collect the following information from participants whilst they are driving.

Mobile phone model and operating system.Latitude and longitude data every 2 s.Vehicle’s speed data every 2 s (measured in metres per second).Duration of the driving trip upon completion.Total distance travelled upon completion of the trip.

This data is processed using industry partner UA’s algorithms to calculate the ‘DrivePoints’ score per participant.

